#### Data Management

The CHEO Clinical Research Unit Data Coordinating Centre will be used as a central location for data processing and management. Data will be kept private and secured to industry standards for both clinical and patient-sensitive data in Canada. Data for the study will be collected and managed using REDCap [88] tools hosted and supported by the CHEO Research Institute. REDCap is a secure, web-based application designed to support data capture for research studies. Only members of the research team will be granted access to the database. Users will be assigned to *Data Access Groups* that will restrict their rights to viewing and entering data. For monitoring purposes, the study coordinator will be able to view the data. Within the Data Access Group, user privileges will be designated by the study coordinator to ensure that the research team members have only the minimum required rights to perform their duties. All identifying information that is collected will be flagged in the database and removed from data export unless the identifying information is required for statistical analysis (eg, date of birth).

### Statistical Analysis

#### Primary Outcomes

Descriptive statistics will be used to summarize patient baseline characteristics and clinical information. The primary objective of this study is to assess the feasibility outcomes of the trial. This will be done by computing the observed points estimates for each criterion (eligibility, recruitment, adherence, credibility, and retention) and comparing them with our predefined red zone upper limits and green zone lower limits. The 3-tiered progression criteria will be used for each criterion (Textbox 1).

Three-tiered progression criteria where E denotes the observed point estimate (ranging from 0 to 1 for proportions or percentages 0%-100%) [50].
**Progression criteria**
Red (unacceptable): E≤red zone upper limit (*P* value nonsignificant, *P* value≥α)Amber (amend): red zone upper limit<E<green lower limitGreen (acceptable): E≥G lower limit (*P* value significant, *P* value<α)

#### Secondary Outcomes

Mean and SDs will be computed for each collected measure. Pre-post correlations will be generated to assess preliminary evidence of *efficacy signal* for QoL, fatigue, symptoms, resiliency, self-efficacy, cognition, anxiety, depression, and mindfulness.

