### Secondary Research Objectives

The **s**econdary research objectives were as follows:

Establish the participants’ expectancy toward both interventions.Examine the participants’ satisfaction with the interventions.Generate estimates to inform sample size calculations for a future multicenter RCT.Assess whether there is preliminary evidence of an efficacy signal for QoL, fatigue, symptoms, resiliency, self-efficacy, cognition, anxiety, depression, and mindfulness.Examine the experimental group’s baseline characteristics, adherence, and attrition rates in those who chose to continue for an additional 4 weeks compared with those who chose to complete the study at 4 weeks compared with those who were lost to follow-up.Examine the control group’s baseline characteristics, adherence, and attrition rates in those who chose to cross over to the experimental interventions at 4 weeks versus those who chose to complete the study at 4 week versus those who were lost to follow-up.Examine whether the experimental intervention is associated with differential brain-based imaging patterns of functional connectivity, cerebral blood flow, and spectroscopy.Examine safety by examining whether the experimental intervention has increased adverse events (ie, total number) relative to the control intervention.

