## Methods

### Trial Design

The proposed study is a Health Canada–regulated parallel-group (1:1) RCT, where patients within 7 days of a concussion will be randomly assigned to one of the two groups: (1) experimental group (n=35), early introduction of the DTx MBI program and (2) control group (n=35), sham DTx attention-matched comparator intervention. The participants will start the intervention the next day after being enrolled in the study. After 4 weeks, those in the experimental group will be offered the MBI program with 4-week additional education modules. Those who are part of the control group will be offered to cross over to start the DTx MBI. Of the 70 participants enrolled, 60 (86%) consenting participants (n=30, 50% from the experimental group and n=30, 50% from the control group) will be enrolled in neuroimaging, which requires participation in a brain scanning session within 72 hours of enrollment and during week 4 of the study. For a schematic diagram of the trial design, procedures, and stages, refer to the study flow diagram in Figure 1.

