##### Attention, Working Memory, and Executive Function

Attention, working memory, and executive function will be assessed using the National Institutes of Health (NIH) Toolbox Cognitive Battery [64]. The NIH Toolbox is a validated and reliable computerized battery designed to measure executive function, attention, episodic memory, language, processing speed, working memory, and fluid cognition. Previous studies have demonstrated lower working memory, attention, and executive functioning scores after injury in pediatric samples with concussion [65-68]. Moreover, mindfulness has been shown to improve attention, working memory, and executive functioning [26,69,70]. The NIH Toolbox will be administered at the 4-week follow-up.

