## Discussion

First, we will use this study to examine the feasibility of our RCT methods, including delivering a DTx-containing MBI to participants who are acutely or subacutely concussed, and whether we can move to the efficacy trial. Second, to better inform our larger RCT, this study will allow us to estimate the effect sizes of QoL and the symptoms at 4 and 8 weeks after enrollment compared with those randomized to the control group (sham intervention). Third, we will use this study to assess whether MBI induces measurable brain-based effects, that is, examine whether the intervention modulates neuroimaging indicators such as functional connectivity. This trial will offer insight into a cost-effective way to manage pediatric concussion in the acute and subacute phases of injury. This study will help support the development of a future full-efficacy trial to assess the effectiveness of the intervention in increasing QoL and decreasing the concussion symptom burden.

The development of an intervention to increase adaptive interpersonal qualities in acute settings is important for reducing the risk of PSAC. Formal in-person MBIs such as mindfulness-based stress reduction have been shown to increase perceived self-efficacy and teach positive acceptance of change [13]. However, these interventions may not be suitable for a youth population with acute concussion as they are costly and not easily accessible. A brief web-based MBI with guided meditation had positive effects on anxiety, negative mood, perceived stress, and attention in different clinical populations [24-27]. Furthermore, a 3-week RCT using the DTx MBI within *AmDTx* increased stress resilience and attentional control in university students self-described as experiencing mild anxiety [27]. The customization of a novel MBI, designed in collaboration with MBI therapists, patients, and Mobio Interactive, will bring a required concussion treatment into the homes of all patients, with the goal of increasing adaptive skills and cognitive performance, promoting neural recovery, and reducing the risk of PSAC. If found to be effective, DTx MBI holds promise as an accessible and low-risk preventative treatment for youth at risk for prolonged postconcussion symptoms and sequelae.

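### The efficacy signal is tied to pre-post correlations, which do not estimate the MBI-versus-sham difference and cannot be formed for cognition

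*Protocol article*

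**What the plan says.** Two sentences in the protocol article (Statistical Analysis, Secondary Outcomes) cover the clinical secondary measures. The first reads "Mean and SDs will be computed for each collected measure". The second begins "Pre-post correlations will be generated to assess preliminary evidence of" and goes on to an efficacy signal in nine domains: QoL, fatigue, symptoms, resiliency, self-efficacy, cognition, anxiety, depression and mindfulness. No contrast between arms is named. The next subsection, on the nested neuroimaging study, does name a regression model for each imaging outcome.

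These sentences serve two separate items under Secondary Research Objectives: "Generate estimates to inform sample size calculations for a future multicenter RCT", and "Assess whether there is preliminary evidence of an efficacy signal for QoL, fatigue, symptoms" and the other domains. The Discussion says the study will "estimate the effect sizes of QoL and the symptoms at 4 and 8 weeks after enrollment compared with those randomized to the control group".

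Three statements on timing matter here:
- Cognition: "The NIH Toolbox will be administered at the 4-week follow-up". Table 3 likewise shows week 4 only.
- Fatigue: the Fatigue subsection describes a baseline in the ED or on day 1, but the Table 3 row is marked only at weeks 4 and 8.
- Crossover: Trial Design and Follow-Up Procedures offer controls the MBI after week 4.

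**The concern.** The article names a statistic and gives it a purpose that it cannot serve. Within an arm, the correlation between baseline and follow-up does not change if every participant improves, or worsens, by the same amount. A stable, trait-like scale will show a high correlation even if the MBI does nothing. Reported under the label of an efficacy signal, such a value could be carried into the case for the definitive trial. Meanwhile the quantity that the Discussion promises, an effect size against control, has no analysis assigned to it. For cognition the named statistic needs a baseline that is not collected.

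**Working it through.** The article gives no figure for this analysis, so there is none to reproduce. The check is whether the named statistic responds to a treatment effect, and what precision a between-arm estimate would have.

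**Inputs from the article.** Trial Design gives "experimental group (n=35") and "control group (n=35"). The Feasibility Objective paragraph under Statistical Power allows about 20% loss, so 35 × 0.80 = 28 evaluable per arm. **Assumed, because not stated:** baseline to follow-up correlation ρ of 0.3 to 0.7, and true standardised difference d of 0 to 0.8.

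**1. Within one arm.** corr(X, Y + c) = corr(X, Y) for any constant c. On one simulated arm of 28, shifts of 0, +0.5 and −2 all gave r = 0.35146.

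**2. Both arms, simulated.** 4,000 replicates, 28 per arm, unit variances, d added to the MBI follow-up scores. Mean results at ρ = 0.5:

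| True d | r, MBI | r, sham | r, pooled | d from by-arm means and SDs |
|---|---|---|---|---|
| 0 | 0.494 | 0.492 | 0.496 | 0.002 |
| 0.3 | 0.494 | 0.487 | 0.489 | 0.303 |
| 0.5 | 0.491 | 0.493 | 0.480 | 0.512 |
| 0.8 | 0.492 | 0.492 | 0.460 | 0.810 |

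The pattern is the same at ρ = 0.3 and 0.7. The small fall in pooled r follows from r = ρ / √(1 + d²/4); at d = 0.8 this is 0.5 / √1.16 = 0.464. Because d enters squared, benefit and harm of equal size give the same value, and a larger effect gives a smaller correlation. The by-arm means and SDs recover d almost without bias.

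**3. Precision of a between-arm estimate.** 95% half-width in SD units = t(54) × √(2/28) × √(1 − ρ²) = 2.005 × 0.267 × √(1 − ρ²):
- unadjusted: 0.54
- ρ = 0.5: 0.536 × 0.866 = 0.46
- ρ = 0.7: 0.536 × 0.714 = 0.38

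With 1.96 in place of t the values are 0.52, 0.45 and 0.37.

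**4. What the correlations are good for.** A future trial analysed with baseline adjustment needs n per arm = 2(1 − ρ²)(1.960 + 0.842)² / d². For an illustrative d = 0.3, two-sided 5% and 80% power, this gives 175, 159, 131 and 89 per arm at ρ = 0, 0.3, 0.5 and 0.7. The correlation is thus a useful planning input.

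**5. Availability.** A pre-post correlation needs two measurements, and the NIH Toolbox supplies one. For fatigue, the text and Table 3 disagree on whether there are two. For anxiety and depression, the first measurement is said to capture preinjury status, so the correlation there relates preinjury to postinjury scores, which is further still from a treatment effect.

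**The case against.** The strongest reply is that means and SDs are planned for every measure. In a 1:1 randomised trial these give the between-arm effect size as soon as they are split by arm, as the table above confirms. The intent to compare arms is also visible elsewhere: in the Discussion, in the Table 2 footnote on differential credibility, and in the promise to control for SES if it is unbalanced. The article condenses a fuller plan, and the choice of model, covariates and analysis set is commonly left to an SAP. The correlations also serve the sample-size objective.

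Much of this stands. A reader might infer that the effect-size objective cannot be met, or that the trial will report no randomised comparison. The documents do not support either reading, because the planned summaries could yield the comparison. A reader might also infer that the correlations carry no information at all about treatment. That is exact only within an arm under a constant shift: pooled r moves slightly, and effects that vary between participants could alter r. The accurate statement is that r does not estimate the effect.

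What the reply does not remove is the sentence itself. It assigns the signal to the correlations rather than to the means, and it lists cognition. That is a stated method unsuited to its stated purpose, not a detail left for later. If an SAP specifies a between-arm analysis, this sentence conflicts with it.

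The fatigue point is weaker. It rests on one row of a table whose layout may not have survived extraction, and it is a discrepancy to reconcile rather than proof that no baseline exists.

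**Conclusion.** The point holds in this form: the analysis named for the efficacy signal measures rank stability, does not estimate the size or direction of the MBI-versus-sham difference, and cannot be computed for cognition. The effect sizes promised in the Discussion could come from the planned means and SDs, but the text neither says these are by arm nor links them to the signal.

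The promised 8-week comparison has a further weakness whatever statistic is used. Once controls may take up the MBI at week 4, the week-8 difference is no longer a clean contrast of MBI with sham.

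The half-widths of 0.54, 0.46 and 0.38 SD describe the precision of the proposed estimate, not harm from the present wording. They rest on 28 per arm and, for the adjusted values, on assumed correlations of 0.5 and 0.7.

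This is a should-fix. A reader might rate it higher because it concerns efficacy, but progression depends only on eligibility, recruitment, adherence, credibility and retention (Table 2), and none of these is touched.

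**What to change.** Reword the two sentences under Statistical Analysis, Secondary Outcomes, and align the Discussion:

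1. State that means and SDs are reported by arm at each visit.
2. Define the signal as the week-4 MBI minus sham difference, with participants analysed as randomised, adjusted for baseline and sex (the stratification factor), with a 95% CI and no claim of efficacy.
3. Take cognition off the pre-post list and compare arms at week 4 only.
4. Keep the pre-post correlations and SDs, labelled solely as planning inputs for the future sample size.
5. In the Discussion, limit the MBI-versus-sham effect sizes to week 4, or label week 8 as descriptive because of the crossover offer.
6. Reconcile the fatigue baseline between the Fatigue subsection and Table 3 before adjusting for it. If none was collected, treat fatigue like cognition.

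The cost is wording only. The changes use measurements the trial already plans to take. The article reports that data collection is still in progress and that no analysis has been done, so the change can be dated before any results are seen.

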#### Neuroimaging Component: Nested Study

To acquire preliminary data on the association between the interventions and MRI metrics, per-protocol analyses will be conducted. A multivariable linear regression will be performed for each neuroimaging outcome, with age, sex, and handedness (for rs-fMRI) as covariates. If the groups differ at baseline on potentially confounding variables, such as attention-deficit or hyperactivity disorder, anxiety, medication, prior concussion, physical activity, and puberty, these variables will also be entered as covariates in the models. Per-protocol analyses will include only those participants who have adhered to the intervention.

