**Methods:**

This study is a double-blind Health Canada–regulated trial. A total of 70 participants will be enrolled within 7 days of concussion and randomly assigned to receive the 4-week DTx MBI (experimental group) or comparator intervention. Feasibility will be assessed based on the recruitment rate, treatment adherence to both interventions, and retention. All outcome measures will be evaluated before the intervention (within 7 days after injury) and at 1, 2, and 4 weeks after the injury. A subset of 60 participants will undergo magnetic resonance imaging within 72 hours and at 4 weeks after recruitment to identify the neurophysiological mechanisms underlying the potential benefits from MBI training in adolescents following a concussion.

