### Eligibility Criteria

#### Inclusion Criteria

Adolescents presenting to either CHEO’s emergency department (ED) or 360cc after sustaining a direct or indirect mild traumatic brain injury (TBI) will be eligible to participate in this study if they (1) are aged 12 to <18 years; (2) have a diagnosed concussion (by a physician), (3) presented to the ED or 360cc within 7 days of TBI; (4) have a score >4 on the Predicting and Preventing Post-Concussive Problems in Pediatrics (5P) clinical risk score, a prediction rule to identify those at risk of poorer outcomes at 4 weeks postinjury [2]; and (5) are proficient in English [38]. To increase the probability of including adolescents with a true concussion, the adapted version of the American Congress of Rehabilitation Medicine [39] framework will be used [40]. Those with either 1 *highest level of certainty* symptom (dazed, confused, or trouble thinking within minutes after injury, difficulty remembering what happened just before or minutes after injury, and loss of consciousness) or 2 *higher level of certainty* symptoms (nausea or vomiting, headache, dizziness, clumsy or balance problems, blurred or double or change in vision, difficulty concentrating, and sensitivity to light or noise) immediately or within 1 hour of injury will be included.

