#### Exclusion Criteria

Patients will be excluded if they present with TBIs with any of the following: (1) a Glasgow Coma Scale score of ≤13; (2) abnormality on standard neuroimaging studies [41], including positive head computed tomography findings (neuroimaging is not required, but may be performed if clinically indicated); (3) neurosurgical operative intervention, intubation, or intensive care required; (4) multisystem injuries with the treatment requiring hospital admission, operating room, or procedural sedation in ED (hospital admission for observation or management of ongoing concussion symptoms is not an exclusion criteria); (5) severe chronic neurological developmental delay resulting in communication difficulties; (6) intoxication to alcohol or drugs at the time of ED presentation as per clinician judgment; (7) no clear history of trauma as primary event to the concussion (eg, seizure, syncope, and migraine); (8) prior psychiatric hospitalization; (9) inability to obtain written informed consent or assent (eg, language barrier); (10) legal guardian not present (certain forms need to be completed by parents or legal guardians); (11) no internet and mobile or tablet access; and (12) currently in therapy.

In addition, patients will not be included in the magnetic resonance imaging (MRI) component if they present with the following: (1) previous neurological or neurodevelopmental disorder such as epilepsy, intellectual disability, or autism (history of attention-deficit or hyperactivity disorder or learning disability is not exclusionary); (2) previous stroke or transient ischemic attacks; (3) sedation medication (eg, propofol, ketamine, nitrous oxide, midazolam, benzodiazepines, and fentanyl) administered before or during ED visit; (4) inability to be present at the 72-hour (+48 or –48 hours) and 4-week (+5 or –5 days) MRI follow-up visits; and (5) medical contraindications to MRI (eg, claustrophobia, pregnancy, or presence of braces or spacers or other metal implants).

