### Randomization, Blinding, and Allocation

#### Sequence Generation

The CHEO Clinical Research Unit will provide data management services for this study and retain randomization codes. The randomization sequence will be created using R software (version 3.1.1; R Foundation for Statistical Computing) [42] and will be stratified by sex, with a 1:1 allocation using random blocks.

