##### Imaging Measurements

*Imaging measurements* will be acquired within 72 hours of injury and during week 4 of the study on a subset of 60 participants. Each brain scanning session lasts 45 to 60 minutes and includes the following sequences: 3D T1-weighted anatomical scan to measure regional volumes and cortical thickness, resting-state functional MRI (rs-fMRI) to assess functional connectivity features or neural networks, arterial spin labeling to assess perfusion or cerebral blood flow, and magnetic proton spectroscopy in a single voxel in the anterior cingulate cortex to assess metabolite concentrations (ie, glutamate and gamma-aminobutyric acid). Table 3 lists the key imaging parameters.

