#### Neuroimaging Procedures

A subset of 60 participants (30 from each group) will undergo a 45-minute MRI scan at <72 hours and 4 weeks after injury. During the day 1 phone call, participants who have consented to the MRI component of the study will complete the MRI screener and schedule their MRI appointment.

Each scanning session will be approximately 1 hour and will include a high-resolution structural scan, arterial spin labeling, rs-fMRI, and magnetic proton spectroscopy (Table 4).

**Table 4 table4:** Magnetic resonance imaging acquisition.

Image type	Sequence name	Total time (minutes:seconds)	Resolution (mm×mm×mm)	Slices, n	FOV^a^ (mm)	TR^b^ (milliseconds)	TE^c^ (milliseconds)	Other
High-resolution anatomical	MEMPRAGE	5:48	1.0**×**1.0**×**1.0	192	256	2500	1.69, 3.55, 5.41, and 7.27	Flip angle=7; inversion time=1050 milliseconds; phase FOV=100%
rs-fMRI^d^	—^e^	12:08	3.0**×**3.0**×**3.0	40	204	2160	25	Flip angle=70; acceleration factor=2; 334 volumes
ASL^f^	3D ASL (GRACE)	5:37	1.8**×**1.8**×**5.0	34	230	4600	15.56	Perfusion mode=Flow-sensitive Alternating Inversion Recovery-QII; bolus duration=700 milliseconds; inversion time=860 milliseconds, 1060 milliseconds, 1260 milliseconds, 1460 milliseconds, 1660 milliseconds, 1860 milliseconds, 2060 milliseconds, 2260 milliseconds, 2460 milliseconds, 2660 milliseconds, 2860 milliseconds, 3060 milliseconds; average=1
ASL	Calibration image (M0)	0:54	1.8**×**1.8**×**5.0	34	230	7500	15.92	Perfusion mode=Flow-sensitive Alternating Inversion Recovery-QII; bolus duration=700; inversion time=7000 milliseconds; average=1
MRS^g^	PRESS	4:38	40**×**20**×**15	—	—	2000	30	Average=128
MRS	MEGAPRESS	4:36 (×2)	40**×**20**×**15	—	—	2000	68	Average=64

^a^FOV: field of view.

^b^TR: repetition time.

^c^TE: echo time.

^d^rs-fMRI: resting-state functional magnetic resonance imaging.

^e^Not available.

^f^ASL: arterial spin labeling.

^g^MRS: magnetic resonance spectroscopy.

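### The imaging regression does not name time since injury as a covariate, although enrolment delay and scan windows let it vary by days to weeks and the scan anchor itself is stated two ways

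*Protocol article*

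**What the plan says.** The section on the nested neuroimaging component sets out the model: "A multivariable linear regression will be performed for each neuroimaging outcome, with age, sex, and handedness (for rs-fMRI) as covariates". It then allows further covariates if the groups differ at baseline on potential confounders, and gives ADHD, anxiety, medication, prior concussion, physical activity and puberty as examples. The analysis is per protocol and keeps only participants who adhered.

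Four other statements decide how far time since injury can vary:

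- **Entry.** The abstract says "A total of 70 participants will be enrolled within 7 days of concussion and randomly assigned", and the inclusion criteria require that the adolescent "presented to the ED or 360cc within 7 days of TBI".
- **Scan tolerance.** The MRI exclusion criteria refer to the "72-hour (+48 or –48 hours) and 4-week (+5 or –5 days) MRI follow-up visits".
- **Scan anchor.** Trial Design describes the imaging part as one "which requires participation in a brain scanning session within 72 hours of enrollment and during week 4 of the study", and the abstract likewise counts from recruitment. Imaging Measurements says the images "will be acquired within 72 hours of injury and during week 4 of the study on a subset of 60 participants", and Neuroimaging Procedures says the subset "will undergo a 45-minute MRI scan at <72 hours and 4 weeks after injury".
- **Allocation.** The sequence "will be stratified by sex, with a 1:1 allocation using random blocks", so enrolment delay is not balanced by design.

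**The concern.** This is an acute-injury study. Its Background says that the contribution of injury factors to persisting symptoms falls with time, and its Discussion describes participants as acutely or subacutely concussed. Days since injury is therefore a natural candidate for a variable that predicts the imaging outcomes whatever the arm. A model that leaves it out puts that variation into the residual error of a small comparison.

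The conditional clause is a poor safeguard for such a variable. It makes adjustment depend on an observed difference between arms, and the article gives no criterion for that difference. A prognostic covariate earns its place because it predicts the outcome, and it does so whether or not the arms happen to differ.

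The contradictory anchor makes this worse. As written, a reader cannot tell how much time since injury will vary at either scan.

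**Working it through.** **1. The plan's own sample size.** The section on the nested sample size starts from 24 participants (12 per group), doubles for multiple comparisons and allows 20% attrition: 24 × 2 = 48, and 48 / (1 − 0.20) = 60. The stated 60 (30 per group) reproduces exactly. The number expected to remain is 48, or 24 per arm, before any loss to the adherence restriction. The effect size behind the 24 is not given.

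**2. Days from injury to scan.** Enrolment falls on days 0 to 7. The tolerances give 72 h ± 48 h = days 1 to 5 and 28 ± 5 = days 23 to 33 after the anchor.

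| | Scan 1 (post-injury days) | Spread | Scan 2 (post-injury days) | Spread |
|---|---|---|---|---|
| Anchored to enrolment | 0+1 to 7+5 = 1 to 12 | 11 | 0+23 to 7+33 = 23 to 40 | 17 |
| Anchored to injury | 1 to 5 | 4 | 23 to 33 | 10 |

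If the first scan may also be taken on the day of enrolment, its range under the enrolment anchor is days 0 to 12, a spread of 12. The difference between the two rows is the 7-day enrolment window. Under the injury anchor, nobody enrolled more than 5 days after injury could meet the first-scan window, even with the full extra 48 hours.

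**3. What enrolment delay carries.** Assume that delay is uniform over 0 to 7 days, that scan timing is uniform within its window, that the two are independent, and that scans are anchored to enrolment.

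- Variance of delay: 7²/12 = 4.08.
- Scan 1: 4²/12 = 1.33 is added, total 5.42 (SD 2.33 days). Delay is 4.08/5.42 = 75% of it.
- Scan 2: 10²/12 = 8.33 is added, total 12.42 (SD 3.52 days). Delay is 4.08/12.42 = 33% of it.

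**4. Precision.** Take 24 per arm, two-sided α = 0.05, a normal approximation, and the standardised effect that gives 80% power unadjusted: (1.960 + 0.842) × √(2/24) = 0.81. A covariate that explains a share R² of outcome variance scales the SD by √(1 − R²), so power = Φ(2.802/√(1 − R²) − 1.960).

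| Assumed R² | Power |
|---|---|
| 0 | 80% |
| 5% | 82% |
| 10% | 84% |
| 20% | 88% |

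The documents give no R² for any imaging outcome, so this is a range of assumptions and not an estimate.

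**5. Chance imbalance in delay.** Under the same uniform delay (SD 7/√12 = 2.02 days), the 95% bound on the difference in mean delay is 1.96 × 2.02 × √(2/24) = 1.1 days at 24 per arm. If 70% of those 24 adhere (the green limit for adherence in Table 2, used here as an illustration), about 17 remain and the bound is 1.96 × 2.02 × √(2/17) = 1.4 days. A gap of that size could easily go unremarked in a baseline table.

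**The case against.** The strongest reply is that covariate choice is ordinary analysis-plan content, that this is a condensed article, and that the component is exploratory and does not feed the progression criteria. That limits the importance of the point. It does not remove it, because the article itself states a covariate set and a rule for adding to it.

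A second reply is that the list of conditional covariates is open, so time since injury could enter if the arms differed. That is correct, and the always-included set should not be read as closed. What remains is that entry would depend on a noticed imbalance.

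A reader might go further in four ways that the documents do not support:

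- **That scans certainly spread over about 12 and 17 days.** This needs the enrolment anchor. Two sections anchor the first scan to injury, and one of them anchors both, which gives 4 and 10 days.
- **That recruiting site creates the variation and must be a covariate.** The 7-day limit is the same for the emergency department and the clinic, no figure shows a difference in delay between them, and Study Setting places all imaging at one centre on one system.
- **That the estimated effect is biased.** Under 1:1 randomisation, a chance imbalance is part of sampling error and the omission mainly costs precision. Restriction to adherent participants weakens that protection, so bias is possible, but nothing shows it.
- **That the week-4 questionnaire comparisons need the same adjustment.** The section on secondary outcomes plans means, SDs and pre-post correlations and states no between-arm contrast to adjust.

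It also stands that the documents do not tie these MRI measures directly to days since injury. The strength of that relation is assumed here.

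**Conclusion.** The point holds as a modest one about precision, together with a contradiction that needs correcting whatever is decided on the covariate. Time since injury is in neither covariate list. It can vary by about 11 and 17 days at the two scans on the enrolment anchor, or about 4 and 10 days on the injury anchor. The gain from adjusting is about 2 to 8 percentage points of power (80% to 82%–88%) if the covariate explains 5% to 20% of outcome variance at 24 per arm.

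The gain from adjusting for enrolment delay depends on the anchor. If scans are timed from enrolment, delay carries most of the variation at the first scan and about a third at the second, under the uniform assumption. If they are timed from injury, delay determines scan timing much less and the gain would be smaller. The per-protocol restriction is an added reason to adjust, because the arms compared are no longer exactly the randomised ones.

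**What to change.** 1. Reconcile the scan anchor across the abstract, Trial Design, the MRI exclusion criteria, Imaging Measurements and Neuroimaging Procedures, so that one reference point and one set of windows applies to each scan.
2. In the nested neuroimaging analysis, add days from injury to enrolment to the covariates that are always included, whether or not the arms differ on it. It is fixed before randomisation, and the 7-day eligibility rule already requires the injury date.
3. Use days from injury to scan only in a sensitivity analysis. The first MRI is booked in the same call as randomisation and both scans take place afterwards, so their timing could depend on arm or engagement.

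No change is needed to the stratification, and site need not be a required covariate. The cost is a sentence of analysis text, one degree of freedom and no new data. The article says that analysis has not yet been conducted, so the change can still be prespecified.
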